**Table 2 T2:**
[figure not shown]
Steroid treatment and types of visits for the included patients (in case of persistent response, normal CRP and no clinical symptoms).

#### Osteoporosis prevention

3.6.2

Calcium (1200 mg/d) plus vitamin D (800 U/d) and 70 mg alendronate weekly (if Tscore <−1) will be prescribed to reduce risk of fracture.

### Follow-up (study I–IV)

3.7

Detailed follow-up plan is summarized in Table 3.

**Table 3 T3:**
[figure not shown]
Schedule of assessment during the study.

In addition to the mentioned investigations, patients will be invited in a coming investigation to perform a magnetic resonance of aortae, and also heart CT scan after completion of the study, to evaluate the risk of aneurisms, especially in the patients with PET positivity of the large vessels. Furthermore, a PWV measurement will also be done at that time.

### Outcomes

3.8

The primary outcome measure are as follows:1.To evaluate the cumulated prednisolone doses, VAS, patients’ assessment of pain, morning stiffness, VAS for physician evaluation, biochemistry results, that is, ESR, CRP, and fibrinogen, and the eventual number of relapses at baseline and during the first year after treatment initiation (weeks 12, 24, 36, and 48) in patients with PET-positive and PET-negative as described above.

The secondary outcome measures are as follows:1.To elucidate the degree of agreement between PET positivity (vasculitis in the large vessels, and also findings compatible with PMR) and TAB positivity.2.To elucidate the degree of agreement between PET negativity (no signs of vasculitis in the large vessels) and TAB negativity.3.To reveal the prevalence of malignancies in the patients detected by the aim of 18F-FDG PET/CT scan and subsequently compare to the prevalence of malignancies detected by the aim of CXR plus abdominal US.4.To reveal the prevalence of malignancies in the patients detected by the aim of CXR plus abdominal US and subsequently compare to the prevalence of malignancies detected by the aim of 18F-FDG PET/CT scan.5.To evaluate BMI, T score, Z score, LBM, FM, BMD, BMC, FFM, FFMI, and FMI at baseline and after 1 year of treatment initiation.6.To evaluate aortic PWV, upper limb PWV, and aortic augmentation index of included patients at baseline and during treatment (weeks 12, 24, 36, and 48).

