### Primary

2.1

The primary objective of this study is to explore the association of 18F-FDG PET/CT findings and uptake patterns (PET positivity/negativity) and the clinical picture of PMR/GCA.

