### Sample size

3.9

This study is, to the best of our knowledge, the first of its kind; hence, formal power calculations were impossible to conduct due to missing information from previous literature or local clinical daily routine. In this exploratory study, the number of patients to be included was set to 80, which enables the assessment of the primary objective, that is, the difference in the cumulated prednisolone dose within the first year after diagnosis between groups including a respective 95% CI, with sufficient precision. Moreover, 80 patients are deemed appropriate to assess the secondary objectives for hypothesis generating purposes.

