### Statistical analysis

3.12

It is anticipated that 80 participants are likely to be included during a period of 1 year. The results will be considered as significant if *P* value <0.05. Statistical analysis has been discussed below with respect to each individual study.

In study I, data will be descriptive (mean ± standard deviation). Comparisons of the data, between the PET-positive and PET-negative patients, will be made with the Mann–Whitney *U* test or Student *t* test, depending on whether or not the distribution is normal. When comparing 2 binary variables, the chi-square test will be performed. Correlation analysis will be performed with Pearson correlation test.

Study II consists of descriptive statistics and proportions of agreement.

Study III consists of descriptive statistics. Comparisons between groups will be made with McNemar test. The sample size of 80 patients is sufficient to indicate a difference of 15% in detection rate of malignancies with 18F-FDG PET-CT scan as opposed to CXR plus abdominal UL (with a significance level of 5% (1-sided), power of 80%, and assuming discordant proportions of 15% and 0%).^[52]^

Study IV consists of descriptive statistics. Univariate comparisons between groups will be made with the Mann–Whitney *U* test or Student *t* test, depending on whether or not the distribution is normal. When comparing 2 binary variables, the chi-square test will be performed. Analysis of repeated measurements over time will be done by means of mixed linear models, using standard errors that allow for intragroup correlation, relaxing the usual requirement that the observations be independent. Comparison of the above mentioned baseline data, matched by age and sex, will be made, to the extent that these data are available.

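### Section 3.8 makes nine measures primary while section 3.9 makes one primary, and section 3.12 applies P<0.05 without ranking them

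*Protocol article*

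**What the plan says.** Three sections of the protocol article describe what is primary.

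- **2.1 Primary** sets a broad aim: to "explore the association of 18F-FDG PET/CT findings and uptake patterns (PET positivity/negativity) and the clinical picture of PMR/GCA". It names no single measure.
- **3.8 Outcomes** lists, under the primary outcome, cumulated prednisolone dose, VAS and patient-assessed pain, then "morning stiffness, VAS for physician evaluation, biochemistry results, that is, ESR, CRP, and fibrinogen, and the eventual number of relapses at baseline". That is eight measures plus relapses, nine in all. The timing is "at baseline and during the first year after treatment initiation (weeks 12, 24, 36, and 48"), in PET-positive and PET-negative patients.
- **3.9 Sample size** describes 80 patients as enough to assess "the primary objective, that is, the difference in the cumulated prednisolone dose within the first year after diagnosis between groups", with a 95% CI.

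Section 3.12 sets one significance threshold, P<0.05, for all results. For Study I it gives a t test or Mann–Whitney test between PET-positive and PET-negative patients, a chi-square test for binary variables, and Pearson correlation. The sentence "Analysis of repeated measurements over time will be done by means of mixed linear models" stands in the Study IV paragraph only.

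**The concern.** Sections 3.8 and 3.9 cannot both be right about which result is primary. The article does not rank the nine measures, name a primary time point or give a rule for several primary tests. As written, a P<0.05 on any of the nine could be presented as the study's primary finding. The rationale for 80 patients, by contrast, refers to one of them only.

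A separate analysis plan cannot remove this, because the conflict lies between two statements that the article itself makes. At stake is the meaning of the headline result: a pre-specified difference in steroid exposure, or whichever of nine outcomes happens to cross the threshold.

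**Working it through.** **Inputs.** Nine measures and five time points (baseline, weeks 12, 24, 36, 48) from 3.8; threshold 0.05 from 3.12, taken as two-sided because the sidedness for Study I is not stated; 80 patients from 3.9. The correlations below are assumptions, since the document gives none.

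**The plan's own figure.** The 80 patients cannot be reproduced for the primary objective: 3.9 states that no formal power calculation was possible and gives no SD or target CI width. What 80 buys for one difference can be shown in SD units as t(0.975, 78 df) × √(1/n₁ + 1/n₂):

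| PET+/PET− split (assumed) | 95% CI half-width |
|---|---|
| 40/40 | 0.45 SD |
| 30/50 | 0.46 SD |
| 20/60 | 0.51 SD |
| 10/70 | 0.67 SD |

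This only illustrates that the precision argument in 3.9 concerns one between-group difference.

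**One test per measure (mildest reading).** With no true differences and independent tests, the chance of at least one P<0.05 is 1 − 0.95⁹ = 0.370. Simulated null tests (100,000 draws) with a common correlation between measures give:

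| Correlation (assumed) | Chance of at least one P<0.05 |
|---|---|
| 0 | 37% |
| 0.3 | 33% |
| 0.5 | 27% |
| 0.7 | 20% |

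That is 20/5 = 4 to 37/5 ≈ 7 times the nominal 5%.

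**Every visit tested (a possible reading, not a stated one).** 9 × 5 = 45 tests, or 43 if cumulated dose and relapses are not tested at baseline. Under independence, 1 − 0.95⁴³ = 0.890 and 1 − 0.95⁴⁵ = 0.901. Simulating the 45-test grid with correlation both between measures and between visits gives:

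| Between measures (assumed) | Between visits (assumed) | Chance of at least one P<0.05 |
|---|---|---|
| 0 | 0.3 | 88% |
| 0.5 | 0.5 | 71% |
| 0.7 | 0.9 | 36% |

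**After the fix.** One named primary outcome tested once has a 5% chance of a false primary result. If all nine stayed primary with one test each, Bonferroni would need 0.05/9 = 0.0056 per test.

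**The case against.** **The study is exploratory.** The title of Study I and sections 2.1 and 3.9 say so, and no confirmatory claim rests on a family-wise error rate. This softens the consequence. It does not remove the conflict: 3.9 reserves the hypothesis-generating label for the secondary objectives, and 3.12 still declares significance at P<0.05.

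**Testing at each visit is not written.** A reader might infer it from fixed visits, two-sample tests and no longitudinal model for Study I, and then conclude that a chance primary result is about 89% likely. The document does not support stating that as fact. Section 3.12 does not say at which visits, or how many times, each measure is tested, and 89% also needs 43 independent tests. The supportable figure is the one-test-per-measure range.

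**The count of nine could be eight.** Section 3.4.1 groups VAS and pain under well-being without saying what the patient VAS rates. If the two are one measure, the independent figure is 1 − 0.95⁸ = 0.337, which changes little.

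**Lack of baseline adjustment is not an error here.** A reader might want the baseline value as a covariate, or baseline comparisons reduced to description, as in a randomised trial. PET status is a baseline exposure, and its association with presenting features is part of the aim in 2.1. Adjusting it away would change the question.

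**The confidence interval is obtainable.** A t test yields a difference and CI directly, and a shift estimate with CI can accompany Mann–Whitney. The choice of test is therefore no contradiction of 3.9.

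**Some of this is analysis-plan detail.** Handling of missed visits and the model for relapse counts may properly sit in a plan that is not shown, and they are not part of this point.

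**Conclusion.** The contradiction between 3.8 and 3.9 is real and should be resolved. With nine unranked primary measures and one test each, the chance of at least one false primary result is 37% under independence and about 20% to 37% over assumed correlations of 0 to 0.7. These figures assume two-sided tests at 0.05 and no true differences. Testing each visit would raise the chance, but the article neither commits to that nor rules it out.

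Section 3.9 settles less than it may seem to. It refers to groups without naming which PET groups, and to the first year without naming week 48. Section 3.4.1 lists four PET groups, whereas the Study I paragraph of 3.12 compares two. The contrast therefore has to be named along with the measure.

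**What to change.** - **3.8:** make cumulated prednisolone dose over the first year the sole primary outcome, as 3.9 already does. Report it as a difference with 95% CI between two PET groups that the sponsor names. List the other eight measures as secondary or exploratory.
- **2.1:** align the wording of the primary objective with that choice.
- **3.12, Study I:** for the serial measures (VAS, pain, morning stiffness, physician VAS, ESR, CRP, fibrinogen), use the mixed linear model approach already named for Study IV in place of separate two-sample tests at each visit. The Study IV text lists no covariates or interaction, so the sponsor must specify the terms.
- **Baseline:** keep the PET-positive versus PET-negative comparisons as part of the exploratory association question.

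The change should be made before the PET results are disclosed at one year. It costs wording in three sections and needs no new data or patients. The price is that eight measures lose primary status.

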### Sample size

3.9

This study is, to the best of our knowledge, the first of its kind; hence, formal power calculations were impossible to conduct due to missing information from previous literature or local clinical daily routine. In this exploratory study, the number of patients to be included was set to 80, which enables the assessment of the primary objective, that is, the difference in the cumulated prednisolone dose within the first year after diagnosis between groups including a respective 95% CI, with sufficient precision. Moreover, 80 patients are deemed appropriate to assess the secondary objectives for hypothesis generating purposes.

### Recruitment

3.10

All patients with the suspicion of PMR/GCR are referred to the Diagnostic Center, Svendborg Hospital. After primary investigation and evaluation, the eligible patients will be referred to the Rheumatology Department of Svendborg Hospital for formal enrolment in the study. Patients will be informed orally and written about the voluntary nature of the participation and project objectives, content, risks, and benefits. A deliberation time of 24 hours will be considered from submission of the oral and written information to obtain informed consent. Consent statement will be reviewed, signed, and dated by the patient and handed over to the department. The patient receives a signed copy of the consent form and be informed of that he/she can withdraw from the study at any time without any reason nor consequences. A scanned copy of patient consent will be added to the patient electronic hospital record, and one additional copy will be stored in a locked room at the department.

### Data collection

3.11

A PhD student will be responsible for collecting data elements from patient medical records, including: demographic data, vital signs (BP, PR), weight, BMI, results of laboratory tests, ECG, and diagnostic tests (18F-FDG PET/CT scan, CXR, abdominal US, TAB, PWV assessment, and whole-body DXA scan), and also cumulative prednisolone dose. Data will be entered into the University of Southern Denmark Research Electronic Data Capture (REDcap) database twice to minimize data entry errors.

### Statistical analysis

3.12

It is anticipated that 80 participants are likely to be included during a period of 1 year. The results will be considered as significant if *P* value <0.05. Statistical analysis has been discussed below with respect to each individual study.

In study I, data will be descriptive (mean ± standard deviation). Comparisons of the data, between the PET-positive and PET-negative patients, will be made with the Mann–Whitney *U* test or Student *t* test, depending on whether or not the distribution is normal. When comparing 2 binary variables, the chi-square test will be performed. Correlation analysis will be performed with Pearson correlation test.

Study II consists of descriptive statistics and proportions of agreement.

Study III consists of descriptive statistics. Comparisons between groups will be made with McNemar test. The sample size of 80 patients is sufficient to indicate a difference of 15% in detection rate of malignancies with 18F-FDG PET-CT scan as opposed to CXR plus abdominal UL (with a significance level of 5% (1-sided), power of 80%, and assuming discordant proportions of 15% and 0%).^[52]^

Study IV consists of descriptive statistics. Univariate comparisons between groups will be made with the Mann–Whitney *U* test or Student *t* test, depending on whether or not the distribution is normal. When comparing 2 binary variables, the chi-square test will be performed. Analysis of repeated measurements over time will be done by means of mixed linear models, using standard errors that allow for intragroup correlation, relaxing the usual requirement that the observations be independent. Comparison of the above mentioned baseline data, matched by age and sex, will be made, to the extent that these data are available.

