## Introduction

1

Polymyalgia rheumatica (PMR) is the most common inflammatory rheumatic disease that affects individuals over the age of 50 years. The typical symptoms of PMR are bilateral aching and stiffness in selected muscle groups, predominantly in the neck, shoulders, upper arms, and pelvic girdle that are most pronounced in the morning and improve with physical activity.^[1–3]^ Giant cell arteritis (GCA) is an inflammatory vasculopathy that typically involves medium and large arteries.^[4]^ Though involvement of the extracranial branches of the carotid artery can be identified in the classic cranial GCA, GCA may also involve aorta and its major branches, predominantly branches of the proximal aorta, that is, subclavian, axillary proximal brachial arteries, representing a subset of patients with large-vessel GCA (LV-GCA).^[4,5]^ Vasculitis, if untreated, can result in ischemic complications, such as ischemic optic neuropathy, which is responsible for vision loss in 10% to 15% of patients. Whereas the etiology of PMR/GCA is still unknown, genetic and environmental factors may play roles in the development of PMR/GCA. GCA and PMR share many pathogenetic and epidemiological features, and are frequently thought to represent different spectrums of the same clinical entity. Despite the high association between PMR and GCA, it is essential to differentiate these 2 conditions due to different steroid treatment regimes. Corticosteroids are considered the treatment of choice for PMR/GCA, with higher doses required for GCA.^[1–3]^ PMR/GCA is generally not associated with reduced longevity; however, patients with aortic aneurysm/dissection have higher rates of mortality.^[6]^ Additionally, patients are at risk of different comorbidities, both due to the disease characteristic itself and also due to treatment side effects.

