#### Study IV: consequences of steroid treatment for BMD, body composition, and also vasculitis/vascular stiffness in polymyalgia rheumatica and giant cell arteritis patients: 1-year prospective study

3.4.4

Patients who are diagnosed with PMR/GCA are at high risk of osteoporosis due to both disease inflammatory process and corticosteroid treatment. Nonspecific bone protection (lifestyle intervention) should be initiated at the time of steroid therapy, and specific antiosteoporotic therapy soon thereafter in patients with low BMD. The gold standard for the diagnosis of osteoporosis is regional dual energy X-ray absorptiometry (DXA) of the hip and spine. Whole-body DXA can estimate 3 body compartments consisting of fat mass (FM), lean body mass (LBM), and bone mass. DXA is currently considered the gold standard for body composition assessment. Changes in whole body bone mineral content (BMC) is a biological meaningful measure of overall calcium balance over a time period, whereas changes in regional BMD are probably more predictive for fracture risk. Changes in body composition due to inflammatory process have previously been reported in rheumatoid arthritis.^[41–43]^ Patients with PMR/GCA are also exposed to different changes in body compositions mainly due to inflammatory process; however, this has not been evaluated before.

The vasculitis process in patients with classic cranial GCA preferentially involves the extracranial branches of the carotid artery; however, large vessel involvement of the aorta and its primary and secondary branches may be involved in patients with LV-GCA.^[4]^ The extent of large artery involvement of GCA is uncertain, but clinically apparent large-vessel disease comprises an estimated 9% to 14% of cases. ^[44,45]^ LV-GCA patients have symptoms and signs of vascular insufficiency and are usually diagnosed with delays due to atypical manifestations, and also inadequacy of GCA criteria for classifying these patients.^[4]^

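### Choosing the test by a normality check does not secure the stated primary estimate: a difference in cumulated prednisolone dose with a 95% CI

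*Protocol article*

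**What the plan says.** Section 3.9 (Sample size) of the protocol article identifies the primary objective as "the difference in the cumulated prednisolone dose within the first year after diagnosis between groups including a respective 95% CI, with sufficient precision". That precision is the only reason given for the sample size on the primary comparison. The section reports that "formal power calculations were impossible to conduct due to missing information from previous literature or local clinical daily routine", and then that "the number of patients to be included was set to 80".

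Section 3.12 (Statistical analysis) plans means with standard deviations for study I. It says that PET-positive and PET-negative patients will be compared by Mann–Whitney U or Student t, "depending on whether or not the distribution is normal". It names no estimator or interval to go with the Mann–Whitney test, does not say how normality is judged, and does not mention unequal variances. Results are called significant at P < 0.05.

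Two other places bear on the point. Section 1 (Introduction) says "Corticosteroids are considered the treatment of choice for PMR/GCA, with higher doses required for GCA", and both conditions are enrolled together. Section 3.4.1 (Study I) forms the groups from the scan result, so their sizes are observed and not set by design.

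**The concern.** The quantity that justifies 80 patients is an estimate with an interval. The analysis rule is a choice between two tests made after looking at the data, and the two branches do not deliver the same thing.

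- **Mann–Whitney branch.** The test compares ranks. On its own it gives a P value, with no difference in dose and no interval. It can also reject when the mean doses are equal, if the two distributions differ in spread. Because patients on PMR and GCA regimens are pooled, a skewed or two-humped dose distribution is a realistic prospect, so this branch may well be the one used.
- **Student t branch.** The test gives the difference in means with a CI, but the standard error pools the two variances. If the groups differ in both size and SD, that standard error is wrong, and so are the P value and the interval.

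What is at stake is whether the headline result is the dose difference that the trial was sized to estimate, and whether its interval has the stated coverage.

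**Working it through.** **Inputs.** From the documents: N = 80 and significance at P < 0.05 (two-sided is assumed, since study I does not say). Not in the documents: group sizes and dose SDs. The splits and SD ratios below are therefore assumptions, shown as a range.

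**The plan's own figure.** N = 80 cannot be reproduced, because section 3.9 gives no SD, interval width or group split. What can be computed is the half-width of the pooled 95% CI in SD units, t(0.975, 78 df) × √(1/n₁ + 1/n₂), with t = 1.991:

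- 40 v 40: 1.991 × √(1/40 + 1/40) = 0.445 SD
- 20 v 60: 1.991 × √(1/20 + 1/60) = 0.514 SD

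So the t branch does deliver the stated quantity when its assumptions hold.

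**The t branch with unequal SDs, 20 v 60.** Set the larger group's SD to 1 and the smaller group's to r. The true variance of the difference is r²/20 + 1/60. The pooled formula targets [(19r² + 59)/78] × (1/20 + 1/60).

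- r = 2: true 0.2167, pooled 0.1154. The pooled SE is √(0.1154/0.2167) = 0.73 of the correct one.
- r = 1.5: true 0.1292, pooled 0.0870. Ratio 0.82.
- r = 0.5: true 0.0292, pooled 0.0545. Ratio 1.37.

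Simulation with equal means, normal data and 20,000 runs per setting gives the actual size at nominal 5%:

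| Split | SD ratio (small/large) | Student t | Welch |
|---|---|---|---|
| 20 v 60 | 0.5 | 0.8% | 5.0% |
| 20 v 60 | 1 | 4.9% | 4.8% |
| 20 v 60 | 1.5 | 10.6% | 4.8% |
| 20 v 60 | 2 | 15.1% | 4.8% |
| 40 v 40 | 0.5 to 2 | 4.9–5.1% | 4.8–5.0% |

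The distortion needs unequal sizes and unequal SDs together. Its direction depends on which group is more variable.

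**Does the normality check protect?** No. With Shapiro–Wilk at 5% in each group (an assumed form of the check, 4,000 runs), the two-stage rule has size 10.9% at ratio 1.5 and 15.6% at ratio 2, for 20 v 60. Normal data mostly pass the check and go to the t test.

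**The Mann–Whitney branch.** With lognormal doses of equal mean but different spread (log-SD 0.7 and 0.4), at 40 v 40 and 20 v 60, Mann–Whitney rejected in 15–24% of runs. With identical lognormal distributions (log-SD 0.5) it held at 4.7–5.1%. It is a valid test of identical distributions, but it does not test the difference in mean dose.

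**Limits of the remedy.** Welch is near 5% above because the data are normal. With identical, strongly skewed groups (lognormal, log-SD 0.7) it ran at 10.0% for 7 v 73 and 8.2% for 11 v 69, against 4.6% and 4.9% for the pooled test. When the small group is also the more widely spread one, Welch reached about 11%.

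**The case against.** The best defence is that this is an exploratory study, that choosing a test by normality is conventional and disclosed, and that a condensed article may leave the interval method to a fuller plan. Section 3.9 does commit to a CI. Planned means and SDs would also let a reader subtract the means whichever test is used. This limits the severity. It does not remove the conflict, because the article states a rule, and on one branch the P value it yields does not belong to the difference that section 3.9 promises.

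Several stronger readings are tempting, and the documents do not support them:

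- **That the plan never delivers the difference with a CI.** The t branch does.
- **That unequal group sizes alone mis-size the t test.** With equal SDs the size stays at about 5%.
- **That the vasculitis group will number 7 to 11.** Section 3.4.4 (Study IV) says "clinically apparent large-vessel disease comprises an estimated 9% to 14% of cases", and 9–14% of 80 is 7 to 11. That figure concerns clinically apparent disease, not PET positivity. Section 3.4.1 labels three of its four groups PET-positive, so PET-negative could be the smaller group. Error rates of 14–26% computed at those splits have no basis in the plan.
- **That the error must be inflation.** Higher doses in GCA imply a higher mean, not a larger SD. Treating clinicians are blinded to the scan, and the Discussion says PET cannot assess the temporal artery, so patients on GCA doses may sit in the larger, vessel-negative group. The t test would then be conservative.

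**Conclusion.** The point holds in limited form. The stated primary quantity and the stated analysis rule do not match: the Mann–Whitney branch produces no dose difference or interval and tests something else, while the t branch produces both but relies on equal variances that nothing in the design assures.

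The size of the t-branch error cannot be known from the article. At an assumed 20 v 60 with normal data it runs from about 1% (smaller group half as variable) to about 10–15% (1.5 to 2 times as variable), and there is no error with equal SDs or equal groups. These figures illustrate the sensitivity and are not a forecast.

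The consequence is moderate, because study I is declared explorative. It should still be corrected: results are to be called significant at P < 0.05, and the sample size rests on this interval.

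**What to change.** In section 3.12, state that for cumulated prednisolone dose, and for other continuous outcomes measured once per patient, the difference in means between PET groups will always be reported with an unequal-variance (Welch) 95% CI, without a prior normality check. Add a bootstrap interval if doses are skewed. Give Mann–Whitney with a Hodges–Lehmann shift and its CI as a sensitivity analysis.

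This costs one sentence and needs no further patients or data. There are two downsides to state. The interval is wider than the pooled one when the small group is the more variable, which is its proper width. Welch is also not exact under strong skew: with only about 7–11 patients in one group it can itself run at about 8–11%, which is why the bootstrap and rank-based results should stand beside it.
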